### Outcomes

Patient usability will be evaluated using the SUS [32] collected at the end of the A-B-A experimental trial. The use of SUS has been recently recommended by the FDA, and it has been used to evaluate the usability of similar technologies. For this study, a nominal SUS score of 68 or higher will be considered as our target score. The feasibility of ARMS will be measured by whether ARMS could significantly increase alcohol abstinence. Other outcomes will include patient adherence to and compliance with the ARMS app considering (1) the proportion of participants that complete the experiment, (2) the proportion of breathalyzer samples submitted, and (3) the proportion of EMA questions answered during the trial. Additional secondary outcomes will include the efficacy of ARMS considering (1) self-reported alcohol use (ATFB), (2) levels of alcohol craving (AUQ), and (3) overall life-functioning (ASI, BSI, and HRQoL). Finally, we will explore whether and how the ANA framework responses collected thrice daily with EMA correlate with alcohol use or abstinence. For instance, we expect that the information captured with the EMA and breathalyzer results will allow the identification of specific mood and state traits that may predict future relapse and, thus, enable the development of personalized relapse prevention strategies.

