**Objective:**

In this paper, we present a full description of our integrated contingency management system, Automated Reinforcement Management System (ARMS), and describe a protocol that will evaluate its feasibility and usability.

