**Methods:**

Initially, 6 clinicians will participate in a 1-hour focus group where the study staff will navigate through ARMS as it would be used by clinicians and patients. Clinicians will provide feedback on the intervention in general, which will be used to modify ARMS to make it more user friendly, time saving, and relevant to treatment. A second focus group will summarize the changes made following the initial clinician feedback and will provide additional input regarding the potential utilization of ARMS. Thereafter, the clinicians’ acceptability of ARMS will be evaluated using the System Usability Scale. Following the clinicians’ assessments of ARMS and final modifications, the system will be evaluated in terms of feasibility and patient usability by using an A-B-A within-subject experimental design wherein 20 treatment-seeking individuals with alcohol use disorder will be recruited. The two A phases (control conditions) will each last 2 weeks, and the B phase (contingency management condition) will last 4 weeks. During all phases, participants will be asked to use the ARMS app to submit three breathalyzer samples per day (at 10 AM, 2 PM, and 8 PM). Participants will be prompted by the ARMS app at these predetermined times to record and submit their breathalyzer samples. During the A phases, participants will earn vouchers for every breathalyzer sample submitted, independent of their sample results. During the B phase, vouchers will be provided contingent upon the submission of alcohol-negative breathalyzer samples (breath alcohol content = 0.00). At the end of the A-B-A experiment trial, patients’ usability of the ARMS app will be evaluated using the System Usability Scale. Feasibility will be measured based on whether the ARMS app helped significantly increase alcohol abstinence.

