## Methods

### Participants

This study will be conducted within the community and with community clinic partners in Spokane, WA, USA, under the auspices of the Washington State University Program of Excellence in Addictions Research at the Analytics and PsychoPharmacology Laboratory. In this phase 1 study, a total of 6 clinicians and 20 patients will be recruited. Patients of either biological sex who are 18 years of age or older and have an Alcohol Use Disorders Identification Test (AUDIT) [22] score of 8 or higher will be eligible to enroll in the study. Participants must read and speak English and have the ability to provide written informed consent. Patients with severe AUD or a co-occurring psychotic disorder according to the Diagnostic and Statistical Manual of Mental Disorders, Fifth Edition (DSM-V) [23], with significant risk of dangerous alcohol withdrawal (defined as a history of alcohol detoxification or seizure in the last 12 months and expression of concern by the individual about dangerous withdrawal), or with a lifetime suicide attempt or suicidality in the past year will not be eligible for enrollment in the study.

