Once the modifications are made in response to the second wave of clinician feedback, ARMS will be evaluated primarily for efficacy but also for feasibility and patient usability through an A-B-A (or, “return-to-baseline”) completely within-subject experimental design. Following similar single subject-design studies conducted by our group [20,24], the two A phases will each last 2 weeks and the B phase will last 4 weeks, for a total study duration of 8 weeks. During all phases, participants will be asked to use the ARMS app to submit breathalyzer samples at 10 AM, 2 PM, and 8 PM each day. Submission of each sample should take less than 5 minutes. Participants will be prompted by their ARMS app to record and submit their breathalyzer samples at these predetermined times and will have a half-hour window following the prompt to submit each sample. During the A phases (control conditions), participants will earn US $2 in vouchers for every breathalyzer sample submitted during the predetermined period, independent of their sample results. Notably, this reward system will be in effect for both the first and second A phases. During the B phase (contingency management condition), vouchers will be provided contingent upon the submission of alcohol-negative breathalyzer samples—that is, breath alcohol content (BAC) = 0.00. Participants will begin by receiving vouchers worth US $2 per alcohol-negative breath sample submitted, with the value escalating by US $0.25 per alcohol-negative sample submission to a maximum value of US $3.50 per submission. Vouchers will be reset to US $2 per sample if a participant does not submit a sample in the predetermined period, if an alcohol-positive breath sample is submitted, or if the participant cannot be identified from the facial recognition photo (see details below).

At the end of the A-B-A experiment trial, the patients’ acceptability of ARMS will be evaluated with the System Usability Scale (SUS).

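### Feasibility is defined by a significant rise in abstinence, an efficacy result, while completion and app use do not enter the feasibility conclusion

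*Protocol article*

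**What the plan says.** The abstract's Objective names two aims, to "describe a protocol that will evaluate its feasibility and usability". Study Design orders the aims of the patient stage differently: "ARMS will be evaluated primarily for efficacy but also for feasibility and patient usability". That wording treats efficacy and feasibility as separate things and puts efficacy first.

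Outcomes then gives the only criterion for feasibility: "The feasibility of ARMS will be measured by whether ARMS could significantly increase alcohol abstinence". The abstract's Methods paragraph says the same: "Feasibility will be measured based on whether the ARMS app helped significantly increase alcohol abstinence". The repetition means that this is not a slip in one place.

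Three measures of delivery and use follow in Outcomes under other outcomes: the proportion of participants completing, the proportion of breath samples submitted and the proportion of EMA questions answered. None is linked to the feasibility conclusion. Usability is handled separately, with a System Usability Scale target of 68 or higher.

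On size and design, Participants says "In this phase 1 study, a total of 6 clinicians and 20 patients will be recruited" and Study Design says "the two A phases will each last 2 weeks and the B phase will last 4 weeks, for a total study duration of 8 weeks". In the A phases a voucher is paid for every sample submitted on time, whatever its result. In the B phase only alcohol-negative samples are paid.

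**The concern.** A feasibility study asks whether the system can be delivered and whether patients will use it. The stated rule asks whether drinking fell by enough to reach significance in a small sample. The two answers can differ in either direction: patients may use the app faithfully while the contrast misses significance, or the contrast may be significant while few samples arrive.

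The Discussion expects the study to supply the information needed to develop a phase 2 trial. A feasibility label that does not reflect completion or use is a poor input to that step. The differing statements of the main aim add to the problem, because a reader cannot tell which result the study stands or falls on.

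**Working it through.** **No figure to reproduce.** The article gives no test, alpha, effect size, SD or dropout for the 20 patients. The figures below are a sensitivity range under stated assumptions.

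**Inputs from the article.** There are 20 patients. On sampling, "participants will be asked to use the ARMS app to submit breathalyzer samples at 10 AM, 2 PM, and 8 PM each day". The A phases total 2 + 2 = 4 weeks and B is 4 weeks, so the scheduled samples per patient are 3 × 28 = 84 in A and 84 in B, or 168 in all. Over 20 patients this is 20 × 168 = 3360.

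**Step 1: a well-used system labelled infeasible.** Assume a paired t-test of B against pooled A on each patient's abstinent proportion, two-sided at 5%. Let dz be the mean within-person difference divided by its SD. Then

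power = 1 − F(t*; n−1, δ) + F(−t*; n−1, δ), with δ = dz·√n,

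where F is the noncentral t distribution function and t* is the 97.5% point of t on n−1 degrees of freedom.

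| dz | Power, 20 completers | Not significant, 20 completers | Power, 16 completers |
|---|---|---|---|
| 0.3 | 24.7% | 75.3% | 20.3% |
| 0.5 | 56.5% | 43.5% | 46.5% |
| 0.66 | 79.9% | 20.1% | 69.4% |
| 0.8 | 92.4% | 7.6% | 84.8% |
| 1.0 | 98.9% | 1.1% | 96.2% |

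Power of 80% needs dz = 0.66 with 20 completers (0.58 if one-sided) and 0.75 with 16. With 20 completers an observed dz below t*/√20 = 0.47 fails the test. None of these figures depends on how well the app was used, except through the number of completers.

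**Step 2: the same on the abstinence scale.** I simulated 4000 trials per scenario, with 20 patients and 84 scheduled samples in A and in B. Assumed: 70% abstinence in A for the typical patient, a between-patient SD of 1.0 and an SD of change of 0.5 (both on the logit scale), and about 95% of samples submitted. A rise from 70% to 75% was significant in 30% to 32% of trials, so it was missed in about 70%. A rise from 70% to 78% was significant in 69% to 72%, so it was missed in about 30%. Each range covers two ways of treating missing samples.

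**Step 3: a poorly used system labelled feasible.** The same model, with no change in drinking between phases:

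| Assumed submission | Overall submitted | Significant if missing = not abstinent | Significant if only submitted samples count |
|---|---|---|---|
| 20% in A, 35% in B | 28% | 100% | 1.5% |
| 30% in both, but positive samples in B at 10% | 28% | 2.1% | 98.8% |
| 2% in both | 2% | 2.1% | 2.6% |

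In the first row the criterion is met by a shift in submission, in the second by withholding positive samples. The change in payment between A and B makes selective submission plausible. Each route works under one missing-sample rule and not under the other. At near-zero use, significance occurs only at about the chance rate.

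**The case against.** The strongest case against is that this is a labelling matter. The three adherence measures are prespecified and will be reported, so a reader can judge use whatever abstinence is called. Nothing in the article makes phase 2 conditional on the abstinence test. The missing-sample rule, the test and alpha may sit in a full protocol or analysis plan that is not shown. The Introduction reports that remote breathalyzer contingency management has been effective, so a large effect is possible and power could be ample.

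Much of this stands and limits the point. A reader might be tempted by stronger claims that the documents do not support:

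- *A usable system could be called unusable.* No: usability has its own criterion on the System Usability Scale. The wrong label would be infeasible.
- *An unused system could be called feasible.* Not beyond chance, as the last row of Step 3 shows. The claim holds for poor use, and then only under some missing-sample rules.
- *A well-used system fails some fixed share of the time.* The 43.5% applies only at dz = 0.5, and the article gives no reason to prefer that value. Nor is dz a between-person effect size: 0.66 × √(2(1−r)) is 0.51 between-person SDs if the A–B correlation r is 0.7, and 0.78 if r is 0.3 (both correlations assumed).
- *Outcomes contradicts Study Design by making efficacy secondary.* The sentence beginning "Additional secondary outcomes will include the efficacy of ARMS considering" goes on to self-reported use, craving and functioning, not breath abstinence. That is compatible with breath abstinence as the main efficacy measure. The real mismatch is between the abstract's Objective and Study Design.
- *Twenty patients is too few.* For a feasibility study that number is not a fault in itself.

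The objection does not remove the rule itself. It is stated twice, it is the only feasibility criterion given, and an unseen plan would not change what the article says.

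**Conclusion.** The point holds. As written, feasibility is decided by an efficacy result alone, although Study Design treats the two as distinct, and the article is inconsistent about which aim comes first. The chance that a well-used system is labelled infeasible runs from about 75% at dz = 0.3 to about 8% at dz = 0.8, given the assumed paired two-sided 5% t-test and 20 completers. The opposite error is shown to be possible at about 28% submission, but its probability cannot be fixed without the missing-sample rule. The fault lies in tying the feasibility conclusion to the abstinence test. It does not lie in the sample size or in the absence of statistical detail from an article.

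**What to change.** 1. In the abstract and Outcomes, define feasibility by the three measures already listed: completion, samples submitted (of 168 scheduled per patient) and EMA questions answered. Report each with a 95% CI against a progression value that the sponsor sets. Recruitment had already begun in January 2021, so date the change and make it before outcome data are examined.
2. Read the progression values as guidance together with the interval, not as hard cut-offs. For illustration only, a rule of at least 16 of 20 completing would fail with probability P(X ≤ 15 | 20, 0.8) = 37% when true completion is 80%, and an observed 16/20 has an exact 95% CI of 56% to 94%.
3. Report the B versus A abstinence contrast as preliminary efficacy: the mean within-person difference with 95% CI. A test may be kept, but not as the feasibility criterion.
4. Make the abstract's Objective and Methods, Study Design and Outcomes state one hierarchy of aims.

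The cost is wording and the setting of three values. No data, visits or patients are added. The downside is that the abstinence result no longer gives a yes/no answer on feasibility.

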## Results

Recruitment for this study began in January 2021. Data collection will be finalized by December 2021, and we expect to publish our results by the second semester of 2022.

## Discussion

### Principal Findings

There currently exists a gap in our knowledge of how to best treat people who wish to reduce their alcohol use, especially in a real-time manner and among those dwelling in areas where access to in-person treatment may be challenging. It is well understood that contingency management is one of the most effective interventions for substance use disorders; however, contingency management has not been widely applied in the field of AUD treatment, in part, because of the difficulty of detecting alcohol abstinence using standard breath alcohol test procedures [15,38]. Our study capitalizes on recent technological advances and clear collaboration potential between academia and start-up companies to partner and develop a smart phone-based contingency management application enabling remote delivery adjunctive treatment for individuals seeking outpatient treatment for AUD.

This phase 1 project will provide baseline capability for the implementation of a remotely monitored contingency management platform. The clinician and user feedback will provide insight into enhancements that can increase utilization and effectiveness. Future capabilities may include (1) adaptation of report-back thresholds to address heavy drinking in addition to abstinence, (2) customization of report-back windows to accommodate user schedules, (3) multimodal reminders (SMS, email, etc) for users and trusted caregivers, (4) geolocation-related alcohol use reporting, and (5) enhanced feedback based on correlations of multiple data points with alcohol use. After completion of this study, we plan to have the necessary information to develop a phase-2 effectiveness trial.

### Limitations

This study has some potential limitations that should be noted. First, in this current stage, ARMS was developed to be used in iOS only. Although this decision was decided strictly due to our budget, we intend to build ARMS for Android as part of our phase 2 trial. Second, this study did not include formal focus groups with the participating patients to evaluate the acceptability and suggestions for improvements by participants. We intend to incorporate such focus groups as part of our phase 2 trial.

## Abbreviations

ANA: addiction neuroclinical assessment
ARMS: Automated Reinforcement Management System
ASI: Addiction Severity Index-Lite
ATFB: Alcohol Timeline Follow Back
AUD: alcohol use disorder
AUDIT: Alcohol Use Disorders Identification Test
AUQ: Alcohol Urge Questionnaire
BAC: blood alcohol content
BSI: Brief Symptom Inventory
DSM-V: Diagnostic and Statistical Manual of Mental Disorders, Fifth Edition
EMA: ecological momentary assessment
FDA: Food and Drug Administration
HL7: Health Level Seven
HRQoL: 15D Health-Related Quality of Life
SUS: System Usability Scale
